**Null hypothesis**

Taking metformin during pregnancy does not affect the likelihood of developing preeclampsia among women with diabetes.

1. **Background**

Metformin is an oral hypoglycaemic agent prescribed to women in pregnancy with pre-existing Type II diabetes and gestational diabetes. It has well-described benefits for mother and neonate when used in this context [22]. Beyond diabetes, metformin has been reported to reduce the likelihood of pregnancy complications among women with polycystic ovary syndrome [23, 24], and in women with previous unsuccessful attempts at in vitro fertilisation (IVF) [25].

Compared with insulin, two meta-analyses concluded that metformin administration is associated with lower rates of preeclampsia[22], and pregnancy-induced hypertension [8]. However, in women with diabetes, studies in this area have been small. Population-based research with larger numbers could generate stronger evidence to better investigate this relationship.

The objective of this research is to determine the relationship between metformin and hypertensive disorders of pregnancy (preeclampsia, eclampsia, gestational hypertension) among women with diabetes, using a national population-based cohort from Scotland.

1. **Study population**

The population will include all nulliparous singleton pregnancies with a diagnosis of diabetes (gestational diabetes or Type II diabetes), recorded in the Scottish Morbidity Records between 2009 and 2018. The Scottish Morbidity Records hold data relating to pregnancy, delivery and perinatal outcomes for all women and infants discharged from maternity hospitals across Scotland.

Exclusion criteria:

a) Multifetal pregnancy

b) Parous women (to account for clustering)

c) Missing gestational age (which will be used to calculate gestational age at exposure)

**Exposure**

Maternal metformin use during pregnancy will be identified through the Scottish National Prescribing Information System (PIS), which has been linked with the Scottish Morbidity Records. Metformin use will be further categorised as use ever, 0 – 12 weeks, 13 – 27 weeks, and 28 weeks onward. Metformin exposure will be assessed for timing, with only prescription prior to preeclampsia diagnosis included.

1. **Primary outcomes:**

Diagnosis of preeclampsia identified by codes O11, O14 and O15 according to the International Classification of Disease Tenth Revision.

Preeclampsia will be further classified by stratifying according to gestational age at birth; <37 weeks and <34 weeks.

Secondary outcomes:

- Gestational hypertension ICD-O13
- Neonatal birthweight: small for gestational age at birth or large for gestational age at birth (defined according to **1)** < or > 2 SD; adjusted for gestational age and offspring sex or **2)** birthweight centile calculated using GROW charts; <10^th^ percentile for SGA and >90^th^ percentile for LGA) (binary)
- Macrosomia; birthweight >4500g (binary)
- Neonatal intensive care unit admission (obtained via neonatal indicator variable)
- Major congenital abnormality (binary)
- Congenital renal anomaly (binary)
- Perinatal death (binary)
- Preterm birth

1. **Additional analyses:**

- Metformin exposure for any indication, compared to the total unexposed population (whether or not they were diagnosed with diabetes)
- It is anticipated that most women requiring metformin in pregnancy will have been prescribed this in the context of Gestational Diabetes or Type II diabetes. The main analysis has therefore been limited to diabetic women, to eliminate diabetes as a confounder
- By number of scripts filled for metformin (possibly reflects compliance)
- By dose, categorised as 1g and >1g

1. **Outline of statistical analysis**
   1. Descriptive analysis

Summary statistics of baseline characteristics of patients will be presented with mean (SD) used to describe normally distributed continuous variables, median (IQR) for skewed continuous variables, and n (%) for categorical variables. Univariate analyses will be performed for each of the variables of interest to be included in the model.

Population characteristics to be described for:

a) Overall cohort

b) Metformin exposed vs non-exposed cohort

| Characteristic | Descriptor | Total population | Metformin exposed | Metformin unexposed |
| --- | --- | --- | --- | --- |
| **Age,** (years) | mean ±SD |  |  |  |
| **Age >35 years** | n (%) |  |  |  |
| **Body mass index** (kg/m^2^) | mean ± SD |  |  |  |
| **Body mass index >30mg/kg** | n (%) |  |  |  |
| **Ethnicity** | n (%) |  |  |  |
| **Smoking,** yes | n (%) |  |  |  |
| **Deprivation score**  1  2  3  4  5 | n (%) |  |  |  |
| **Pre-gestational disorders**  Hypertension  Cardiovascular disease  Autoimmune diseases  Diabetes  Type I  Type II  Renal disease | n (%) |  |  |  |
| **Year of birth**  2009  2010  2011  2012  2013  2014  2015  2016  2017  2018 | n (%) |  |  |  |
| **Gestational diabetes** | n (%) |  |  |  |

- 1. **Outcome analysis**

Potential estimators are (i) selection model, using inverse probability weighting (IPW); (ii) outcome model, using regression adjustment; (iii) doubly robust inverse probability weighted regression adjustment (IPWRA) models. Under correct specification, all the estimators should produce similar results. We will focus on IPWRA; selection model will be included in the IPW and outcome in regression (RA) model specification. We will combine both regression adjustment and augmented IPW in a doubly robust regression model. We will also perform RA, IPW and multivariate LR separately.

Model for exposure assignment using inverse probability weighted propensity scores derived from the logistic exposure model. Adequacy of balance achieved by PS weighting will be assessed using: (i) standardised mean difference for model covariates and variance estimates between exposure groups and (ii) propensity scores overlap. If unbalanced, we will explore measures such as: addition of interaction terms; different exposure models; use of alternate weighting structures (overlap or stabilized); and lastly propensity score-based trimming with the aim of achieving overlap if the propensity score distributions.

This will be performed for the overall cohort and then subgroup analyses will be performed.

The model will be created for each outcome with the final included covariates determined by the authorship team and informed by direct acyclic graphs (Fig S1, S2). Covariates to be considered:

1. Maternal age at delivery
2. Body mass index
3. Deprivation score
4. Ethnicity
5. Smoking status
6. Pre-existing maternal disease
7. Conception with assisted reproduction

All statistical analysis will be performed using StataSE version 17.0.

- 1. Handling of missing data

a. Consideration of missing data will be confined to all the covariates identified for the construction of a (propensity score) model of the exposure status. When imputing these missing covariate values the imputation model will include all those identified for inclusion in the propensity score model as well as additional covariates. These co-variates will be selected once the data are available for review.

b. Multiple imputation will be performed using chained equations, and the imputed datasets will then be used for propensity score construction. Subjects with missingness greater than 50% of PS_covariates will be excluded from analysis, this proportion will be assessed and if substantial, may result in changes to the PS_covariate list used for ongoing analysis.

c Diagnostics will then be performed to assess the quality of the imputed datasets.

d. The number of imputed datasets will be set at a minimum of 20 with the number increased to equal to the highest percentage of missingness in the raw PS_covariate list (ceiling of 50% by design). For each of these imputed datasets IPWRA will be calculated and Rubin’s rule will be used pool parameters of estimate. Details of imputation and assessment of adequacy will be formally presented.

If imputation is unsuccessful, a complete case analysis will be used.

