**Appendix**

**Table S1: Coding of covariates and outcome variables**

| **Clinical characteristic** | **Method of ascertainment** | **Description** |
| --- | --- | --- |
| Preeclampsia | ICD O11.1-5, O11.9 | Pre-existing hypertension with preeclampsia |
|  | ICD O14.0-2, O14.9 | Preeclampsia including HELLP syndrome |
|  | ICD O15.0-2, O15.9 | Eclampsia |
| Hypertensive diseases of pregnancy | ICD O13.1-5, O13.9 | Gestational (pregnancy induced) hypertension without significant proteinuria |
|  | ICD O11.1-5, O11.9 | Pre-existing hypertension with preeclampsia |
|  | ICD O14.0-2, O14.9 | Preeclampsia including HELLP syndrome |
|  | ICD O15.0-2, O15.9 | Eclampsia |
| Chronic hypertension | O10.0-4, O10.9 | Pre-existing hypertension complication pregnancy and the puerperium |
|  | ICD O11.1-5, O11.9 | Pre-existing hypertension with preeclampsia |
|  | ICD I10 | Essential (primary) hypertension |
|  | Check-box coding in the Swedish Medical Birth Register | Coded during antenatal care in response to “Chronic hypertension”, coded: “Yes” |
| Systemic lupus erythematosus (SLE) | Check-box coding in the Swedish Medical Birth Register | Coded during antenatal care in response to “SLE”, coded: “Yes” |
| Kidney disease | Check-box coding in the Swedish Medical Birth Register | Coded during antenatal care in response to “Kidney disease”, coded: “Yes” |
| Polycystic ovarian syndrome | ICD E28.2 | Polycystic ovarian syndrome |
| Gestational diabetes | ICD O24.4 | Gestational diabetes |
|  | Check-box coding in the Scottish Morbidity Records | In response to “Mother’s status of diabetes”, coded: “Yes, Gestational diabetes (diagnosed during pregnancy)” |
| Type 2 diabetes | E24.1 | Pre-existing type 2 diabetes mellitus, in pregnancy, childbirth and the puerperium |
|  | E11.0-9 | Type 2 diabetes mellitus |
| Congenital anomaly (neonatal) | Coded in the Scottish Morbidity Record | In response to “Congenital anomaly”, coded: “Acute life-threatening” “Non-life threatening” or “Yes” |
| Neonatal intensive care unit admission | Coded in Scottish Morbidity Record | In response to “Neonatal indicator”, coded: “Admitted for up to 48 hours” or “Admitted for more than 48 hours” |
| Neonatal death | Coded in Scottish Morbidity Record | In response to “Outcome of pregnancy”, coded: “Livebirth dying within the first six days of life” or “Livebirth dying on or after the 7^th^ day but before the 28^th^ day” |

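### For women who enter through gestational diabetes, the 0–12 week metformin contrast can condition on a diagnosis made after exposure, and it mixes them with Type II women without a split by diabetes type

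*SAP*

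**What the plan says.** **Entry.** Study population takes "all nulliparous singleton pregnancies with a diagnosis of diabetes (gestational diabetes or Type II diabetes". Table S1 identifies gestational diabetes by an ICD code or by a Scottish check-box answer, "Yes, Gestational diabetes (diagnosed during pregnancy". Neither gives a date or week of diagnosis.

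**Exposure.** The Exposure section reads: "Metformin use will be further categorised as use ever, 0 – 12 weeks, 13 – 27 weeks, and 28 weeks onward".

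**Ordering.** The one timing rule is "Metformin exposure will be assessed for timing, with only prescription prior to preeclampsia diagnosis included". Gestational age is required in order to date the exposure; the exclusion is "Missing gestational age (which will be used to calculate gestational age at exposure". Nothing orders the script relative to the diabetes diagnosis.

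**The drug and its other uses.** Background describes metformin thus: "Metformin is an oral hypoglycaemic agent prescribed to women in pregnancy with pre-existing Type II diabetes and gestational diabetes". It adds that "metformin has been reported to reduce the likelihood of pregnancy complications among women with polycystic ovary syndrome", and also mentions women with failed IVF attempts. Table S2 carries polycystic ovary syndrome as a Scottish covariate.

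**Reason for the restriction.** Additional analyses explains that the main analysis is limited to diabetic women so that diabetes cannot act as a confounder. The same section plans a comparison of exposure for any indication with all unexposed women, diabetic or not. That comparison is not specified by window.

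**Adjustment.** Outcome analysis lists age, BMI, deprivation, ethnicity, smoking, pre-existing maternal disease and assisted reproduction. Subgroup analyses are promised but not named.

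**The concern.** Restricting to diabetic women removes confounding by diabetes only where the diabetes comes before the exposure. That holds for pre-existing Type II diabetes. It need not hold for gestational diabetes when the script falls in weeks 0–12. A woman given metformin early for another reason is in the cohort only if gestational diabetes is later recorded; if it is not, she is absent. The early-exposed women who remain would be those diagnosed despite the drug. If metformin lowers the chance of diagnosis, they carry a higher average underlying risk than unexposed women with the same diagnosis. When that underlying risk also raises the risk of preeclampsia, a null drug looks harmful.

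A second problem sits on top of this. Type II women already have an indication in early pregnancy, so they can be expected to supply most early use, while the unexposed group contains women with gestational diabetes. Without a split or adjustment by diabetes type, the early-window contrast is partly a comparison of diabetes types.

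At stake is the reading of the 0–12 week result, and to a lesser degree of the 'ever' result, which contains the same women.

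**Working it through.** The plan gives no figure to reproduce here, so the check is a reading of the order of events, followed by an illustration of size.

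**1. Order of events**

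| Route into the cohort | When eligibility arises | Can a 0–12 week script come first? |
|---|---|---|
| Pre-existing Type II | before pregnancy | no |
| Gestational diabetes | during pregnancy, week not given | yes, unless diagnosis precedes the script |

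The rule on preeclampsia orders exposure and outcome. It does not order exposure and entry.

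**2. Do the planned methods repair it?** Propensity weighting, overlap checks and trimming act on women already selected, so they cannot restore early users who were never diagnosed. Pre-existing maternal disease might be read to include Type II diabetes, but this is not stated, and the Scottish column of Table S2 shows no diabetes-type row.

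**3. Illustration A (logistic).** All inputs are assumptions. A is early metformin and U ~ N(0,1) is an unmeasured metabolic risk.

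- P(gestational diabetes) = expit(−3 + b1·U + ln(OR)·A)
- P(preeclampsia) = expit(−3.7 + b2·U), with no effect of A
- Spurious RR = P(preeclampsia | gestational diabetes, A=1) / P(preeclampsia | gestational diabetes, A=0), integrated over U

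Selected results:

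| OR of A on diagnosis | b1 | b2 | Spurious RR |
|---|---|---|---|
| 1.0 | any | any | 1.000 |
| 0.8 | 0.5 | 0.5 | 1.003 |
| 0.6 | 1.0 | 0.8 | 1.037 |
| 0.5 | 1.5 | 0.8 | 1.089 |
| 0.4 | 1.5 | 0.8 | 1.116 |

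In the last row the preeclampsia risks among diagnosed women are 0.0758 with early use and 0.0679 without, so 0.0758/0.0679 ≈ 1.12. Over 30 combinations (OR 0.4, 0.5, 0.6, 0.7, 0.8; b1 0.5, 1.0, 1.5; b2 0.5, 0.8) the range is 1.003–1.116 and the median 1.025. One cell exceeds 1.10.

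**4. Illustration B (probit threshold).** Assumed: prevalence of gestational diabetes 3% or 10%; share of diagnosis liability due to the unadjusted risk 0.2–0.8; preeclampsia RR 1.22–1.65 per SD of that risk; true metformin RR 1.00.

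| RR of diagnosis under early metformin | Spurious RR for preeclampsia |
|---|---|
| 1.00 | 1.00 |
| 0.49–0.57 | 1.02–1.12 |
| 0.22–0.30 | 1.05–1.27 |

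The last row needs metformin to prevent some 70–78% of diagnoses, so it is an extreme.

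**5. Dilution into 'ever' use.** Suppose a fraction p of exposed women are early users with gestational diabetes, the other exposed women have RR 1.00, and baseline risk is equal. Then RR(ever) ≈ 1 + p·(RR − 1). The documents do not give p. With RR 1.116:

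- p = 0.05: 1 + 0.05 × 0.116 = 1.006
- p = 0.20: 1 + 0.20 × 0.116 = 1.023

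With the extreme 1.27 and p = 0.20: 1 + 0.20 × 0.27 = 1.054.

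These figures cover the selection mechanism only. Confounding by diabetes type in the pooled window is not quantified, because no risks by type are given.

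**The case against.** The strongest reply is that the bias needs two facts the documents do not state: that gestational diabetes is diagnosed after the early script, and that early metformin lowers the chance of diagnosis. Without the second, the spurious RR is exactly 1.00. This stands, and it makes the conclusion conditional.

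The reply on size also stands in large part. The bias is mostly a few per cent, and the illustrations leave the metabolic risk wholly unadjusted although BMI and age are planned covariates. In these models it runs toward apparent harm, so this mechanism would not create the hypothesised protection. The weighted preeclampsia interval in Table S4 (two or more scripts, a different contrast) is 0.47–1.95, far wider than any value above. But a small bias beside a wide interval does not make the early contrast interpretable, and precision does not bear on the mixing of diabetes types.

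A reader might infer more than the documents support:

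- That the early window is invalid outright. Type II women are unaffected, and so is a woman diagnosed before her early script.
- That gestational diabetes offers almost no overlap at 0–12 weeks. No counts by window are given, nor a comparator for each window. If such users were very few, they would also carry little bias.
- That missing any benefit gained by preventing gestational diabetes is an error. The question is posed among women with diabetes, so this is a matter of estimand.
- That the main result is materially distorted. The number of early off-indication users is not given. The raw standardised difference for polycystic ovary syndrome in Scotland, 0.07, gives no sign that they dominate the exposed group.
- That starting exposure at week 13 cures the problem. A script from week 13 can still precede diagnosis.

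The any-indication analysis is a partial answer, since it does not select on diabetes. But it is not planned by window and leaves the main-cohort contrast as it is.

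**Conclusion.** The point holds in a limited form. For women without pre-existing diabetes, the plan lets the 0–12 week exposure precede the diagnosis that admits them, and nothing in the planned adjustment removes the resulting selection. In those women the contrast is causally interpretable only if early metformin does not change who is diagnosed. The pooled window is also open to confounding by diabetes type.

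On assumed inputs the spurious RR from selection is about 1.00–1.12, toward apparent harm; only if metformin prevented most diagnoses does it reach 1.27. The effect on 'ever' use is probably small, about 1.006–1.023 if 5–20% of exposed women were affected at an RR of 1.116. These figures rest on the assumed effect on diagnosis and on an unmeasured shared risk factor, neither of which the documents give. The change is worth making because it is cheap, not because the main result has been shown to be wrong.

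**What to change.** 1. Interpret the 0–12 week window only in women with pre-existing Type II diabetes, whose eligibility comes before exposure.
2. Report the 'ever' and later-window results by diabetes type. Table S1 already codes the two types separately.
3. Add a sensitivity analysis of the 'ever' result that excludes women with gestational diabetes whose first script was at 0–12 weeks, shown beside the result that includes them.
4. Where a date of gestational diabetes diagnosis is available, count exposure in these women from that date, not from a fixed week 13. If it is not available, say so as a limitation.
5. Report early use in women without pre-existing diabetes by window within the any-indication analysis, which does not select on diabetes.

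The cost is SAP wording and subset re-runs, mostly on data already planned; item 4 depends on a date that the documents do not show to exist. The price is a smaller sample and a wider interval for the 0–12 week window.

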**Research question**

Among women with diabetes, is metformin associated with a reduced likelihood of preeclampsia?

Main analysis

Overview

P–Nulliparous diabetic (gestational diabetes or Type II diabetes) women with a birth recorded in the Scottish maternity and neonatal birth record between 2009 and 2018

I–Prescription of metformin during pregnancy

C–No prescription of metformin during pregnancy

O–Hypertensive disorders of pregnancy

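### The exposure cut-off at preeclampsia diagnosis is not limited to the hypertensive outcomes, so it also sets exposure for the neonatal outcomes and conflicts with the plan's own comparator

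*SAP*

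**What the plan says.** The overview under Research question (SAP, Additional File 1) sets two groups: "I–Prescription of metformin during pregnancy" and "C–No prescription of metformin during pregnancy". Neither refers to preeclampsia.

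The Exposure section takes prescriptions from the linked national prescribing data. "Metformin use will be further categorised as use ever", and by three gestational windows. It then adds the timing rule: "Metformin exposure will be assessed for timing, with only prescription prior to preeclampsia diagnosis included". This is the only timing rule, and it names no outcome to which it is confined.

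The secondary outcomes follow: gestational hypertension, SGA/LGA, macrosomia, NICU admission, major congenital abnormality, congenital renal anomaly, perinatal death and preterm birth. None has an exposure definition of its own.

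The Outcome analysis section lets the model differ by outcome: "The model will be created for each outcome with the final included covariates determined by the authorship team". Exposure is not said to differ. Preeclampsia is not among the candidate covariates.

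**The concern.** For preeclampsia itself the cut-off is reasonable, because a prescription issued after diagnosis cannot have prevented the disease. For the neonatal outcomes the mother's diagnosis is the wrong limit, because the fetus can be exposed until birth.

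In the ever-versus-never contrast, the women affected are those whose first metformin prescription follows a preeclampsia diagnosis. A woman with an earlier prescription stays exposed. Those affected lose exposed status only because they have preeclampsia, which can itself change the risk of NICU admission, preterm birth, SGA and perinatal death. Exposure status then depends on a cause of the outcome. The propensity weighting does not repair this, since the listed covariates do not include preeclampsia, and as a later event and a study outcome it could not serve as a baseline covariate.

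At stake are the neonatal safety comparisons, and whether two analysts would build the same groups from this text.

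**Working it through.** **1. Where a post-diagnosis starter falls**

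| Text | Exposed? | Comparator? |
|---|---|---|
| Overview | Yes: prescribed during pregnancy | No |
| Exposure section | No: her prescription is not counted | Not stated |
| Exclusion criteria | Not excluded | Not excluded |

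She is in the study population with no countable prescription, so coding her unexposed is the natural default. That contradicts the overview's comparator. Dropping her would need a rule that the plan does not give.

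**2. Inputs for the size**

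- Table S4: preeclampsia in 18 of 637 women with at least two scripts and in 77 of 2,672 unexposed. Check: (18/637)/(77/2,672) = 0.98, as printed.
- Number of post-diagnosis starters, k: not given. If all sit in the Table S4 unexposed column, the ceiling is 77/2,672 = 2.9%.
- Outcome risk without and with preeclampsia: not given. Assumed 10% vs 20% or 40% for an adverse outcome, 20% vs 10% for a large baby, and 3% vs 3% for an unrelated outcome.
- Metformin has no effect within preeclampsia strata.

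Table S4 compares at least two scripts with none, so it only illustrates.

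**3. If prescribing is unrelated to preeclampsia**

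Take the Table S4 counts as the groups before the cut-off, with preeclampsia nearly balanced. The rule moves k women with preeclampsia from exposed to unexposed. At 10% vs 40%:

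- Expected events, exposed: 619 × 0.10 + 18 × 0.40 = 69.1.
- Expected events, unexposed: 2,595 × 0.10 + 77 × 0.40 = 290.3.
- Before the rule: (69.1/637)/(290.3/2,672) = 0.998.
- After it, k = 4: (67.5/633)/(291.9/2,676) = 0.978, a shift of −0.021.
- After it, k = 1: (68.7/636)/(290.7/2,673) = 0.993, a shift of −0.005.

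At 10% vs 20% the same steps give shifts of −0.002 (k = 1) and −0.007 (k = 4). For a large baby, k = 4 gives +0.004. For the unrelated outcome the shift is zero.

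**4. If the groups are balanced after the cut-off**

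Now take Table S4 as already classified and ask what other codings would give, at 10% vs 40%:

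| k | Left unexposed | Moved to exposed | Dropped |
|---|---|---|---|
| 4 | 0.998 | 1.019 | 1.002 |
| 8 | 0.998 | 1.040 | 1.007 |
| 77 (ceiling) | 0.998 | 1.399 | 1.085 |

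Example, k = 4 moved: ((69.1 + 1.6)/641)/((290.3 − 1.6)/2,668) = 1.019. For a large baby, moving runs the other way: 0.996 at k = 4 and 0.933 at k = 77.

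**5. Reading the two together**

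Under both premises, coding these women unexposed gives a lower RR than coding them exposed when preeclampsia raises the outcome risk. Which coding lies nearer the null depends on whether metformin starts are related to preeclampsia, and the documents do not say. Exclusion is not neutral. Under step 4 it gives 1.002 at k = 4. Under step 3, dropping the same four from the exposed group gives (67.5/633)/(290.3/2,672) = 0.981.

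**6. Against sampling error**

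At 10% risk in both groups, SE of log RR = √(9/637 + 9/2,672) = 0.132, so the crude 95% CI around 1.00 is about 0.77 to 1.30. A shift of 0.02 lies far inside it.

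**The case against.** Three objections have force.

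First, scope. The rule names preeclampsia, and the research question and null hypothesis concern preeclampsia, so the authors may have meant it for that analysis only. That may be so, but no sentence says it, and the neonatal outcomes have no other exposure definition.

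Second, coding. The plan does not state that post-diagnosis starters are unexposed, and the overview's comparator argues against it. This stands: coding them unexposed is the likely reading, not a stated rule. The conflict remains whichever coding was intended.

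Third, recoding can itself mislead. Women who start after diagnosis bring the risk of preeclampsia into the exposed group, and step 4 shows RRs above 1 with no metformin effect. This also stands, but it depends on the groups being balanced after the cut-off. If prescribing is unrelated to preeclampsia, as in step 3, the before-birth definition is the less biased one.

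A reader might infer that the plan makes metformin look safer on every neonatal outcome. It does not: the direction depends on how preeclampsia relates to each outcome. A reader might also move 4, 8 or 15 women at the Table S4 preterm share (30/77) against a 10% background, obtain RRs of 1.02, 1.05 and 1.08, and call these the true values. They are not. Those counts have no source in the documents, and that calculation contains no metformin effect, so the excess comes only from moving preeclampsia cases between groups.

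**Conclusion.** The point holds as a defect of definition. One outcome-specific cut-off governs all outcomes as written, it contradicts the overview's groups, and the classification of women first prescribed after diagnosis is left open.

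If they are coded unexposed, RRs are lowered for outcomes that preeclampsia makes more frequent. The direction can reverse for LGA and macrosomia, and nothing changes for outcomes unrelated to preeclampsia. The likely size is small: about 0.002 to 0.02 on the RR for 1 to 4 affected women. This rests on assumed counts, assumed outcome risks, no metformin effect and metformin starts unrelated to preeclampsia. The documents do not supply the count, so a larger effect cannot be ruled out, but nothing in them supports one. The primary preeclampsia analysis is not called into question by this point.

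**What to change.** In the Exposure section:

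1. Limit the pre-diagnosis cut-off to the hypertensive outcomes.
2. For the neonatal outcomes, define exposure as in the overview: any metformin prescription during pregnancy, before birth. Hold it as a second flag.
3. State how women first prescribed after a preeclampsia diagnosis are classed for each outcome group, and report how many there are.
4. Show the neonatal results with these women coded exposed, coded unexposed and excluded.
5. For preterm birth, assess exposure up to a fixed gestation or as time-updated, because early birth shortens the time available to start metformin.

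Items 1 to 4 cost a few sentences, a second flag from data already linked, and repeat runs of the planned models. Item 5 is more work if the time-updated route is taken, since the planned logistic exposure model with weighting compares two fixed groups. A fixed-gestation definition is simpler.

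The downside is that post-diagnosis starters may carry the risk of preeclampsia, and neither recoding nor exclusion fully removes it. The three codings show how far the result depends on these women and should be reported as that, not as a correction.
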